#### Demographic and Medical Information

Age, ethnicity, gender identity, sexual orientation, marital and parental status, years of education, income, occupation, reproductive health history, and medications will be assessed using a survey created for this study.

#### Primary Outcome

Fertility-related quality of life was assessed using the 24-item Core FertiQoL [24], yields 4 subscales: mind-body, relational, social, and emotional. High scores on the FertiQoL scale indicate a better quality of life. It is the most widely used infertility-specific measure of quality of life [25] and has been well validated in multiple studies [20]. This primary outcome was chosen in collaboration with our patient advisors as it provides an integrated measure of the emotional, physical, and interpersonal impacts of infertility.

#### Secondary Outcomes

Secondary outcomes will include depressive and anxious symptoms, instances of mood and anxiety disorders, relationship quality, and health care use. Treatment adherence and acceptability will also be assessed.

#### Depressive Symptoms

Self-reported symptoms will be assessed using the PHQ-9 [26], a 9-item measure assessing symptoms in the last 2 weeks that closely parallels the criteria for major depressive disorder as defined by the *Diagnostic and Statistical Manual of Mental Disorders, Fifth Edition* (DSM-5) [27]. Internal consistency coefficient (ICC) has been estimated at α=.89 and test-retest reliability at r=0.84. The PHQ-9 has been shown to be superior to other questionnaires in detecting changes in depressive mood following treatment [28]. Participants endorsing suicidal ideation on item 9 of the PHQ-9 will be required to answer a weekly question.

#### Anxious Symptoms

Self-reported symptoms will be assessed using the GAD-7 [29], a 7-item measure that asks about symptoms in the last 2 weeks and closely parallels the DSM-5 criteria for generalized anxiety disorder. ICC is α=.92. The GAD-7 has been shown to be superior to other questionnaires in detecting change in anxious mood following treatment [30].

#### Mood and Anxiety Disorders

These will be assessed using NetSCID (TeleSage), the computerized version of the Structured Clinical Interview for the DSM-5 (SCID). Though the originally funded protocol proposed to use the Primary Care Evaluation of Mental Disorders (PRIME-MD), we decided to switch to the SCID because of the availability of the computerized version of this interview. The SCID is also the gold standard assessment for psychiatric diagnoses.

#### Relationship Quality

Relationship quality will be measured through the 7-item Relationship Assessment Scale. Internal consistency among individuals with infertility has been found to be high, with α=.83 [31].

#### Health Care Use

The questionnaire on health care consumption and productivity losses for patients with a psychiatric disorder will be administered 16 weeks following the intervention, asking participants to report on health care use in the last 4 months. This survey has shown good agreement with hospital- and employer-confirmed data. An additional section has been added to specifically ask about the receipt of fertility treatments.

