**Methods:**

We will recruit 170 individuals struggling to become pregnant in Canada or the United States to be randomized to our 7-week self-help program or a treatment-as-usual condition. The primary outcome will be fertility quality of life, while secondary outcomes will include depressive symptoms, anxious symptoms, and relationship quality, assessed before and after the program as well as biweekly for 16 weeks following completion of the program. Self-reported health care use and the presence of diagnosed mood and anxiety disorders, assessed through a structured psychiatric interview, will also be assessed immediately following the intervention and at the 16-week follow-up assessment. Treatment adherence and retention will also be recorded throughout the intervention. Multilevel modeling will compare the intervention arm to the treatment-as-usual condition in terms of all continuous outcomes across the 9 measurement points. Logistic regression will be used to assess the occurrence of mood and anxiety disorders in the 2 treatment arms at the posttreatment assessment as well as at the 16-week follow-up. Sensitivity analyses will examine potential treatment moderators: membership in the LGBTQIA+ (lesbian, gay, bisexual, transgender, queer, intersex, and asexual) communities, baseline fertility quality of life, cultural background, disability status, and pursuit of conception through medical intervention.

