**Results:**

We expect our intervention to be more effective than treatment-as-usual in improving all mental health parameters assessed and decreasing health care use related to both mental and reproductive health. Effects are expected to be larger with decreasing baseline quality of life and equally effective regardless of membership in the LGBTQIA+ communities, cultural background, or disability status.

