### Participants

#### Inclusion and Exclusion Criteria

Based on our sample size calculations, we will recruit 170 women, recruited through the web. The inclusion criteria will include the following: is infertile as defined as either actively attempting to conceive for ≥12 months without success or is currently undergoing fertility treatments (eg, ovulation induction medication, IVF, and intrauterine insemination). This definition ensures that this study is inclusive of both individuals who cannot afford fertility treatments and women who are in same-sex couples and cannot conceive naturally. Though the original funded protocol excluded individuals reporting active suicidal ideation, those already receiving psychotherapy, and those with high levels of fertility-related quality of life (FertiQoL above 70), we have since decided to remove these exclusion criteria in order to closely estimate the program’s anticipated real-world effectiveness. Rather than exclude individuals based on baseline quality of life, we will perform secondary analyses, considering baseline quality of life as a treatment moderator.

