### Primary and Secondary Outcomes

#### Overview

Self-reported psychological outcomes will be assessed immediately postintervention (ie, at the end of the 7th week) and every 2 weeks for 16 weeks. Mood and anxiety disorders will be assessed immediately postintervention as well as 16 weeks postintervention. Finally, health care use will be assessed at postintervention week 16. The control group will follow an identical outcome assessment schedule.

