## Discussion

### Significance of the Study

It is expected that participants assigned to the Coping with Infertility program will exhibit improved fertility quality of life as well as depressive and anxious symptoms, with moderate to large effect sizes. We also expect rates of clinical mood and anxiety disorders as well as self-reported health care use to be lower among participants randomized to the treatment arm. Baseline fertility quality of life is furthermore expected to moderate the effect of treatment such that effect sizes will increase with decreasing baseline fertility quality of life. Based on the pilot study results, we expect adherence and retention to be favorable. If our hypotheses are confirmed, these findings would suggest that the Coping with Infertility program is more effective than currently available psychological interventions for infertility. Indeed, a recent meta-analysis by our team identified 58 randomized controlled trials testing psychological interventions for infertility and found that, with the exception of trials conducted in the Middle East, interventions were associated with only small psychological benefits, highlighting the need for more effective interventions [16]. The self-help nature of the Coping with Infertility program also likely makes it more cost-effective than individual psychotherapy, which typically costs US $100-$200 per session.

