If our intervention proves effective, we will aim to make our mobile app publicly available through the Apple Store and Google Play Store. Decreased health care use in the treatment arm relative to the treatment-as-usual arm would provide a strong rationale for seeking government funding to upkeep the Coping with Infertility mobile app, which would allow us to make the program available free of charge. We would provide flyers and posters to fertility clinics across North America, to be posted in clinic waiting rooms and physician offices. We will reach out to relevant professional societies and nonprofit organizations, asking them to include the app as a mental health resource listed on their website. Online forums relevant to infertility will also be contacted and asked to share information related to the app. A YouTube channel will be created to house all of the weekly module videos along with a professionally produced animated explainer video introducing the intervention and describing the results from the trial supporting its efficacy. Final, we will publish our findings in open-access journal articles in respected scientific journals.

In addition to disseminating the Coping with Infertility program as a stand-alone intervention, it may also be worthwhile to pair it with other traditional mental health resources. For example, future research pairing the Coping with Infertility program with infertility support groups, or with individual psychotherapy may help target a broader audience of individuals experiencing infertility-related distress who wish to benefit from peer or therapist support. Translating the content of the program into a workbook format may also appeal to a subset of the target population.

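### Health care use, a secondary outcome, has no baseline measurement, so its between-arm comparison is valid but less precise than it could be, and the stated assessment times conflict.

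*Protocol article*

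**What the plan says.** **Timing.** The Health Care Use section states that the questionnaire "will be administered 16 weeks following the intervention, asking participants to report on health care use in the last 4 months". The Overview under Primary and Secondary Outcomes agrees: "health care use will be assessed at postintervention week 16". The Methods paragraph of the Abstract differs. It says that health care use, together with diagnosed disorders, "will also be assessed immediately following the intervention and at the 16-week follow-up assessment". No section places the questionnaire before randomisation. By contrast, Trial Design says that quality of life, distress, mood and anxiety symptoms and relationship quality are taken both before and after the program.

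**Expectation.** The Results paragraph of the Abstract expects the program to do better than treatment-as-usual in "decreasing health care use related to both mental and reproductive health". Significance of the Study expects "self-reported health care use to be lower among participants randomized to the treatment arm" and adds: "Decreased health care use in the treatment arm relative to the treatment-as-usual arm would provide a strong rationale for seeking government funding".

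**Population and related baseline data.** Inclusion and Exclusion Criteria explains that an earlier exclusion of "those already receiving psychotherapy" has been dropped. The Randomization Scheme stratifies by whether the participant is in fertility treatment. The demographic and medical survey collects reproductive health history and medications.

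**Analysis.** Statistical Analyses puts the baseline value of the outcome into the mixed model for five scales (FertiQoL, PHQ-9, GAD-7, the Copenhagen stress scale and the Relationship Assessment Scale), giving statistical power as the reason. Health care use is not among the five.

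**The concern.** How much care people used before entry usually says a good deal about how much they will use afterwards. In this trial prior use should vary widely: participants may or may not be in psychotherapy, may or may not be in fertility treatment, and may seek other psychological care in either arm. Without a baseline measure, that variation stays in the error term of the between-arm comparison.

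The article values baseline adjustment for the power it gives on its scale outcomes, but the schedule rules out the same gain here. The sample size was set for FertiQoL, so this outcome has no power reserve of its own. The result also carries weight: lower use is to support a request for public funding. A funder may well ask whether the arms used similar amounts of mental health care at entry, and the trial could not answer directly. People lost before week 16 are a further problem. Under the schedule in the Methods they contribute no health care use data at all, and there is no prior use with which to examine whether their loss was related to it.

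**Working it through.** **1. The plan's own figure.** Power Calculations uses Cohen f = 0.25, so d = 2f = 0.5, with alpha 0.05 (two-sided assumed) and 80% power. The normal approximation, n per arm = 2(1.960 + 0.842)²/0.5², gives 63, or 126 in total. The exact t test gives 63.8, so 64 per arm and 128 in total, as stated. For dropout, 128/0.75 = 170.7, against 170 stated. The sample size reproduces, but it concerns FertiQoL. No figure is given for health care use.

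**2. Is there a baseline under any reading?**

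| Place | Assessment of health care use |
|---|---|
| Abstract, Methods | immediately postintervention and at 16 weeks |
| Overview of outcomes | postintervention week 16 |
| Health Care Use | 16 weeks after the intervention, 4-month recall |
| Trial Design (measures taken before and after) | not listed |

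The Abstract's extra assessment would not serve as a baseline, because it follows randomisation. If it also used a 4-month recall (about 17.4 weeks), it would cover the 7 program weeks and 17.4 − 7 = 10.4 weeks before them, mixing use before and after allocation.

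**3. Size of the precision loss.** Let r be the correlation between use in the 4 months before entry and use at follow-up. The documents give no r, so a range is assumed. Adjustment for the baseline value multiplies the residual variance by 1 − r² and the standard error by √(1 − r²). With 64 evaluable per arm, the difference detectable with 80% power is (1.960 + 0.842) × √(2/64) × √(1 − r²), in SD units.

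| r | Variance factor | SE factor | Detectable difference (SD) | Power at d = 0.3 |
|---|---|---|---|---|
| no baseline | 1.00 | 1.000 | 0.495 | 40% |
| 0.4 | 0.84 | 0.917 | 0.454 | 46% |
| 0.5 | 0.75 | 0.866 | 0.429 | 50% |
| 0.7 | 0.51 | 0.714 | 0.354 | 66% |

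The standard error therefore falls by 1 − 0.917 = 8% at r = 0.4 and by 1 − 0.714 = 29% at r = 0.7. The value d = 0.3 is illustrative and does not come from the article.

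**4. Limits of this calculation.** It treats use as a continuous outcome with a linear relation to baseline, whereas utilization data are usually skewed. It also compares adjustment with no adjustment at all. If the analysis already used the stratification factor or baseline symptom scores, the further gain from prior use would be smaller. The percentages are upper values for each r.

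**The case against.** A reader might infer that the trial cannot show the decrease it predicts, because a single later value per person reveals no change. The document does not support that. The Abstract's sentence is a comparison with treatment-as-usual, and Significance of the Study speaks of "Decreased health care use in the treatment arm relative to the treatment-as-usual arm". A randomised comparison of postintervention values estimates that contrast without bias, missing data aside. Only change within a person or within an arm is out of reach, and no section clearly promises it.

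Three other strong readings also fail.

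- That the questionnaire is certainly given only once: the Methods sections say so, but the Abstract says twice.
- That the article breaks its own baseline-covariate rule: the rule covers five named scales, and the analysis of health care use is not described. Such detail may stand in a document that is not shown. The fair statement is that the same reasoning cannot be extended to this outcome.
- That imbalance in fertility care cannot be checked: status at entry is a stratification factor, so it is known before allocation and available as a covariate.

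The strongest form of the objection is that what remains is an optional gain in precision on one of several secondary outcomes, resting on an assumed correlation. Its limits are accepted: validity, the primary outcome and the sample size are untouched, and prior use is a plausible strong predictor rather than a proven one. But the stratification factor is only yes/no and says nothing about prior mental health care. Baseline PHQ-9, GAD-7 and FertiQoL measure symptoms and quality of life, not use.

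**Conclusion.** The point holds as one of precision and consistency, not of bias. Every stated schedule places health care use after the intervention only, so prior use cannot serve as a covariate, and for mental health care nothing else recorded at entry clearly replaces it. For an assumed correlation of 0.4 to 0.7, the standard error without adjustment is higher than it need be: adjustment would lower it by up to about 8% to 29%, and by less if other baseline covariates are used or the data are skewed. The outcome is secondary, but the funding argument built on it and the low cost of the remedy make the change worthwhile. The conflict between the Abstract and the two Methods sections over assessment times does not depend on any assumption and needs to be resolved in any case.

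**What to change.** 1. Give the same questionnaire, with the added fertility-treatment section and the same 4-month recall, at the enrollment session with the other baseline questionnaires, before the allocation envelope is opened. Asking later would not be equivalent, since participants would then know their assignment.
2. Compare the arms on health care use with adjustment for the baseline value and for the fertility-treatment stratification factor.
3. Word the expectation and the result as lower use than under treatment-as-usual, not as a change over time. The Results paragraph of the Abstract needs this most.
4. Reconcile the Abstract with the Overview and Health Care Use sections: one postintervention assessment or two. If two, state the recall period for each.

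The cost is a few more minutes of participant time at enrollment. No new instrument, visit or staff is needed. For anyone already randomised without the questionnaire, the stratification factor and the baseline scales are the available covariates, and the report should say so.

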#### Treatment Adherence

The total number of minutes spent accessing each moule video will be tracked through the mobile app. Homework completion between the weekly module videos will be tracked using Qualtrics, a web-based survey platform that facilitates scheduled survey distribution, notifications, and reminders. Homework compliance will be further measured at the end of each week through the 12 items contained within the Homework Rating Scale, which assesses comprehension of homework assignments as well as effort spent on assignments [32].

#### Treatment Acceptability

The Credibility Expectancy Questionnaire [33] will be administered at baseline to assess participants’ initial expectations about the intervention. Postintervention, the Treatment Acceptability and Adherence Scale [34] will be used to assess treatment acceptance. The Negative Effects Questionnaire [35] will assess any potential adverse events perceived to be related to the intervention. Final, participants will be invited to provide written feedback about any of the modules or the program as a whole, including suggestions for further improvement and refinement.

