#### Preliminary Testing of Our New Infertility-Specific Intervention

With a new program developed and fully vetted in consultation with our patient advisory panel, we conducted a pilot study of 21 women recruited through local support groups, assessing intervention acceptability [19]. All participants exhibited clinically significant levels of infertility-related distress, as indicated by a Fertility Quality of Life Scale (FertiQoL) score ≤52 [20]. Enrolled through a Zoom (Zoom Video Communications)-administered enrollment session, participants received 1 module per week through email and were asked to view the 10-minute slideshow within 24 hours of receipt. Midweek, they received an email reminder of the homework assignment, encouraging them to apply their homework assignment throughout the week. At the end of each week, participants were asked to rate the extent to which the module and homework were perceived as helpful in lowering their distress (0-10). At baseline and each week, participants completed the Generalized Anxiety Disorder-7 (GAD-7) and 9-item Patient Health Questionnaire (PHQ-9); the FertiQoL was completed at baseline and after the intervention. Each week and in an interview at the end of the study, participants provided written and verbal feedback, respectively, on the intervention.

Of the 21 women enrolled in the study, 2 became pregnant and were removed from the program prematurely (all outcomes assessed until the point of pregnancy were analyzed). Of the remaining 19 women, 15 completed all 6 modules, and 4 completed a portion of the program. Data from all 19 women were included in the analysis. The average helpfulness rating of each module was found to be 7.4 or above out of 10. Fertility quality of life increased by an average of 12 points out of 100, translating to a Cohen *d*=0.9. Large reductions in both mean symptoms of anxiety and depressed mood were observed (pre-to-post Cohen *d*=–1.2 and –1.3, respectively, where effects above 0.8 are considered large), corresponding with clinically meaningful improvements. In addition, 85% of participants experienced a clinically significant decline in either anxious or depressive symptoms (defined as a change of 4 points on the GAD-7 [21] and 5 points on the PHQ-9 [22]).

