#### Treatment-As-Usual Control Condition

Participants assigned to the control condition will be instructed to continue their pursuits to conceive without accessing the self-help program. They will be permitted to access other psychological resources that are available to them, though, like the intervention condition, they will be asked to report any treatments accessed in the postintervention survey. They will complete the outcome measures at the same time as participants in the treatment condition. Following completion of the study, the control group will be offered the program in the same manner as the treatment group.

In the original funded grant protocol, we had proposed a waitlist control condition in which participants were not permitted to access other mental health services; however, we have since changed the control condition to treatment-as-usual in order to more accurately estimate the real-world effectiveness of the treatment. This change also allows us to open the trial to individuals reporting suicidal ideation because these participants will likely require additional mental health services while participating in the current trial.

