#### Statistical Analyses

Descriptive statistics will examine treatment acceptability outcomes as well as the trial recruitment rate. A 2-tailed *t* test will be used to compare the treatment arms in terms of baseline characteristics, assessing randomization success. A mixed model design using the MIXED procedure in SAS (version 9.4; SAS Institute) applying an intent-to-treat approach will compare the intervention arm to the waitlist control group in terms of FertiQoL, PHQ-9, GAD-7, Copenhagen Multi-Center Psychosocial Infertility Fertility Problem Stress Scale, and Relationship Assessment Scale (RAS) score across the 9 outcome measurement points (ie, at the end of intervention week 7 and biweekly for 16 weeks). Each outcome will be examined in a separate model; subject will be treated as a random effect, and the treatment assignment will be treated as a fixed effect. A repeated statement will identify assessment week as a repeated measure factor. Baseline levels of the outcome will be included as a covariate. This method has been shown to provide optimal statistical power relative to measuring pre- and postintervention outcome change [36]. In using all available data, a mixed model design has also been shown to outperform ad hoc approaches, such as the last-outcome-carried-forward approach [37].

In addition to examining the main effect of treatment assignment on outcomes, the interaction between assignment and assessment week will be examined to determine whether outcomes are maintained across the 9 postintervention measurements. Sensitivity analyses will use a similar approach to examine potential treatment moderators: membership in the LGBTQIA+ communities, baseline FertiQoL score, cultural background, disability status, and pursuit of conception through medical intervention.

The LOGISTIC procedure will assess the occurrence of mood (major or minor depressive episode or persistent depressive disorder) and/or anxiety disorders (generalized anxiety disorder, social anxiety disorder, or panic disorder) in the 2 treatment arms at the posttreatment assessment as well as at the 16-week follow-up.

To limit the family-wise error rate, the Benjamin and Hochberg [38] false discovery rate correction will be applied to all analyses.

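### The only stated adverse-event measure depends on attribution to the program and is analysed descriptively; no between-arm proportion of participants who worsen is stated, although both arms supply the scores for it

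*Protocol article*

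**What the plan says.** All references are to the protocol article.

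- **Harm instrument.** Treatment Acceptability states that the Negative Effects Questionnaire "will assess any potential adverse events perceived to be related to the intervention". No other instrument is described as measuring adverse events.
- **Its analysis.** Statistical Analyses states: "Descriptive statistics will examine treatment acceptability outcomes as well as the trial recruitment rate". No comparison between arms is given for these outcomes.
- **Control exposure.** Under Treatment-As-Usual Control Condition, controls "will be instructed to continue their pursuits to conceive without accessing the self-help program". They are offered it only once the study is over.
- **Data in both arms.** The Overview of the outcomes section states: "The control group will follow an identical outcome assessment schedule". Statistical Analyses compares the arms on FertiQoL, PHQ-9, GAD-7 and relationship quality at nine postintervention points, with the baseline score as covariate. It also compares the occurrence of mood and anxiety disorders by logistic regression after treatment and at the 16-week follow-up.
- **Individual change sizes.** The pilot report (Preliminary Testing of Our New Infertility-Specific Intervention) counts clinically significant symptom reductions, "defined as a change of 4 points on the GAD-7" and 5 points on the PHQ-9.
- **Population.** On the move from waitlist to treatment-as-usual, the article says: "This change also allows us to open the trial to individuals reporting suicidal ideation". Participant Safety describes weekly risk questions for those who endorse PHQ-9 item 9 at baseline.

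**The concern.** A measure restricted to effects that people ascribe to the program can err in both directions. Distress that would have occurred anyway may be blamed on the program, and worsening caused by the program may be put down to infertility. Only a comparison with the control arm separates the two, and the stated harm measure offers none.

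This matters more here because entry has been widened to include people reporting suicidal ideation. Success would also lead to public release of a self-help app and videos (Discussion, Significance of the Study). The investigators expect smaller effects at higher baseline quality of life, so some participants have less expected benefit to set against any harm. A reader deciding on release would want to know how many people deteriorated in each arm.

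**Working it through.** **Step 1. The plan's own sample size.** Power Calculations gives Cohen f = 0.25, α = .05, power 80% and a total of 128. For two arms d = 2f = 0.5. A two-sided t test has power 0.801 with 64 per arm and 0.795 with 63, so 2 × 64 = 128 reproduces. Allowing for 25% dropout, 128/0.75 = 170.7, against 170 stated (85 per arm). These figures are not in dispute; they supply the 64 and 85 per arm used below.

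**Step 2. Do the controlled analyses already show who worsens?**

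- *Means.* As an illustration with assumed figures, let 85% of treated participants improve by 5 PHQ-9 points and 15% worsen by 5. The mean change is 0.85 × (−5) + 0.15 × 5 = −3.5. The mixed model would report an improvement of 3.5 points, and the 15% would not be visible.
- *Diagnoses.* The structured interview is placed after the intervention and 16 weeks later, and Outcomes Assessment pays for two postintervention interviews. No baseline interview is stated. Occurrence at a time point therefore cannot separate new onset or worsening from a disorder already present at entry.
- *Suicidality.* The weekly question is described for participants who endorse item 9 at baseline. It is not among the listed secondary outcomes and has no comparison in Statistical Analyses. Someone whose ideation begins after baseline is outside that subset.

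**Step 3. What a between-arm proportion would deliver.** The article gives no worsening rate, so 5% to 20% is assumed, equal in both arms. The 95% CI half-width for the risk difference is 1.96 × √(2p(1 − p)/n). For p = 0.10 and n = 64 this is 1.96 × √(0.18/64) = 0.104; for n = 85 it is 1.96 × √(0.18/85) = 0.090. Power is for a doubling of the control rate at two-sided .05.

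| Assumed rate | Half-width, 64 per arm | Half-width, 85 per arm | Power, 64 per arm | Power, 85 per arm |
|---|---|---|---|---|
| 5% | 7.6 points | 6.6 points | 19% | 23% |
| 10% | 10.4 | 9.0 | 35% | 45% |
| 15% | 12.4 | 10.7 | 53% | 65% |
| 20% | 13.9 | 12.0 | 70% | 82% |

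**Step 4. Missing scores.** At the allowed dropout, 85 − 64 = 21 per arm have no score. The expected number worsening among 64 is 64 × 0.05 = 3.2 to 64 × 0.20 = 12.8. The missing would outnumber those seen to worsen, so they have to be reported beside them.

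**The case against.** The best case against runs as follows. The article states nothing false: an attribution-based questionnaire summarised descriptively is a legitimate choice. The arms are compared on baseline-adjusted symptom scores and on diagnosed disorders, which do not depend on self-attribution and extend to the end of follow-up. A deterioration table is often left to an analysis plan, and that plan is not shown.

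Much of this stands, and it rules out several stronger readings that a reader might infer:

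- *That the trial gives no controlled estimate of worsening at all.* Average worsening, or an excess of disorders, would show in the planned comparisons.
- *That controls cannot complete the questionnaire.* The article does not say which arm receives it, and the identical schedule could include controls. The supported point is narrower: controls have no program to attribute effects to, so their answers would not form a meaningful comparator.
- *That the questionnaire is given only at week 7.* The word placing an instrument after the intervention opens the preceding sentence, on a different scale. No timing is stated for this one.
- *That risk goes unmonitored.* Participant Safety sets out a weekly question, an alert and follow-up for those endorsing item 9 at baseline, and says that people with a plan or intent are not enrolled. (Inclusion and Exclusion Criteria says the exclusion for active suicidal ideation was removed. The two sections must be reconciled, but that is a separate matter.)

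The 4- and 5-point changes are also cited for improvement, so using them for worsening is a convention borrowed from the article, not one it validates. Applying the same cut-off in both arms keeps the comparison fair even if the cut-off is imperfect.

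The appeal to an unseen analysis plan does not fully answer the point. The article itself fixes the harm instrument, its reliance on attribution and its descriptive analysis. A better measure is available from data already planned.

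**Conclusion.** The point holds as a cheap improvement to a weak stated method, not as a flaw that undermines the trial. The only stated adverse-event measure yields no meaningful between-arm estimate, and the controlled analyses do not show the proportion of individuals who worsen.

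The gain from adding that proportion is real but limited. The interval half-width would be about 7 to 14 percentage points, and power to detect a doubling would be 19% to 82%, depending on the rate and the number analysed. These figures rest on assumed worsening rates of 5% to 20%, equal rates for the interval widths, and 64 to 85 analysed per arm. It would be wrong to infer that the added outcome could establish safety: a difference near zero would still be compatible with modest harm.

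**What to change.** Keep the Negative Effects Questionnaire as a descriptive measure, and state when it is given and to whom. Add to Statistical Analyses, before results are seen, a descriptive harm outcome in both arms:

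- worsening from baseline of at least 5 points on the PHQ-9 or at least 4 points on the GAD-7, at week 7 and at the 16-week follow-up;
- new endorsement of PHQ-9 item 9 among those who did not endorse it at baseline.

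For each, report by arm the count, the denominator and the number with missing scores, together with the risk difference and its 95% CI. State that this is an estimate outside the false discovery rate family, because the article now applies that correction to all analyses. Say plainly that the interval is wide and that absence of a difference is not evidence of absence of harm.

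The cost is a few lines of text and one table. No new assessment is needed, since both arms already complete both scales at baseline and at all nine postintervention points.
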